#### Secondary outcomes

Secondary outcomes include an alternative categorization of disease-modifying agents (including glucocorticoid therapy), changes in diagnostic imaging (changes in vdHSS, non-contrast modified OMERACT RAMRIS, number of erosions, and proportion of patients with erosions), disease activity (28-joint Disease Activity Score [61], Clinical Disease Activity Index [62], Simplified Disease Activity Index [62], Rheumatoid Arthritis Disease Activity Index [63], Rapid Assessment of Disease Activity in Rheumatology [64], Routine Assessment of Patient Index Data 1-5 [65]), function (Health Assessment Questionnaire [66], Multi-Dimensional Health Assessment Questionnaire [67]), quality of life (Health Utility Index Mark 3 [68], EuroQOL general quality of life instrument [69], EuroQOL general quality of life instrument Visual Analog Scale [69]), healthcare resource utilization and work productivity. Changes from baseline over biannual time points will be investigated. Paired analyses comparing changes in imaging interventions will be conducted. Healthcare resource utilization and work productivity will be determined as adapted from previous work in this population [70]. Healthcare resource utilization will be supplemented by linking patients to provincial healthcare databases. All secondary outcomes are exploratory and therefore hypothesis-generating in nature.

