### Interventions

Study measures are captured in the schedule of assessments (Table 1). Study participants will attend study visits at weeks 0, 13, 26, 39, 52, 78, and 104. All participants will have MRI and X-ray scans within 4 weeks of biannual study visits from weeks 0 to 104. Clinical assessments, prognosis, and response to pharmacologic treatment will be assessed quarterly during the first year and biannually in the second. Study participants will be accrued over 1 year and followed for 2. At week 0 (baseline) and 104 weeks, all study participants will have an MRI conducted for the second to fifth MCPs of both hands. All participants will also have X-rays of both hands and feet conducted at baseline and 104 weeks.

**Table 1 T1:** Study schedule of assessments

**Assessment**	**Week**						
	**0**	**13**	**26**	**39**	**52**	**78**	**104**
Informed consent	X	X	X	X	X	X	X
OHIP number (each visit)	X	-	-	-	-	-	-
Demographics							
Date of birth	X	-	-	-	-	-	-
Gender	X	-	-	-	-	-	-
Race/ethnicity	X	-	-	-	-	-	-
Dominant hand	X	-	-	-	-	-	-
Household income (socioeconomic status)	X	-	-	-	-	-	-
Pack-years smoked	X	-	-	-	-	-	-
Medical history and comorbidities							
Surgeries	X	X	X	X	X	X	X
Conditions	X	X	X	X	X	X	X
Medications	X	X	X	X	X	X	X
Clinical assessment	X	X	X	X	X	X	X
Symptom duration	X	-	-	-	-	-	-
Morning stiffness duration	X	X	X	X	X	X	X
Swollen joint count	X	X	X	X	X	X	X
Tender joint count	X	X	X	X	X	X	X
Extra-articular features	X	X	X	X	X	X	X
Fatigue	X	X	X	X	X	X	X
Pain – Visual Analog Scale	X	X	X	X	X	X	X
Global physician impression of disease progression	X	X	X	X	X	X	X
Global patient impression of disease progression	X	X	X	X	X	X	X
Diagnostic imaging							
MRI – MCPs 2-5							
Worst-affected hand	-	-	X	-	X	X	-
Both hands	X	-	-	-	-	-	X
Radiography							
Both hands	X	-	X	-	X	X	X
Both wrists	X	-	X	-	X	X	X
Both feet	X	-	-	-	-	-	X
Laboratory tests							
Rheumatoid factor	X	O	O	O	O	O	O
Anti-citrullinated cyclic peptide antibodies level	X	-	-	-	-	-	-
Erythrocyte sedimentation rate	X	X	X	X	X	X	X
C-reactive protein	X	X	X	X	X	X	X
Other	X	X	X	X	X	X	X
Concomitant medications	X	X	X	X	X	X	X
Adverse events	X	X	X	X	X	X	X
Health-related quality of life							
Health assessment questionnaire	X	-	X	-	X	X	X
Health Utility Index Mark 3 and EQ-5D	X	-	X	-	X	X	X
Health resource utilization	X	-	X	-	X	X	X
Work and leisure time productivity	X	-	X	-	X	X	X

X, assessment conducted; O, assessment conducted only if preceding assessment negative.

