### Randomization

Minimization (that is, baseline adaptive randomization) will be used to allocate participants to one of the three study interventions. Allocation by minimization is recommended for small sample size clinical trials in diseases with many known prognostic markers [41,42]. The minimization procedure can accommodate 10 to 20 variables without sacrificing statistical power [71,72]. Parameters for minimization will include the following:

● Participant self-reported symptom duration (<6, 6-24, >24 months)

● Baseline 28-joint Disease Activity Score (<2.6, 2.6-3.2, 3.2-5.1, >5.1)

● MRI or X-ray evidence of erosions from the hands, wrists or feet at baseline

● Rheumatoid factor positivity (positive; negative; not available)

● Anti- citrullinated cyclic peptide positivity (positive; negative; not available)

● Extra-articular features of RA

● Health Assessment Questionnaire

● Conventional DMARD treatment

● Biologic DMARD treatment

● Treating rheumatologist

With the exception of 'treating rheumatologist', these variables have prognostic value and are expected to inform DMARD treatment decision-making [43]. ‘Treating rheumatologist’ will be included as a minimization parameter to balance the effect of varying pharmacological disease management standards of care by physician across the three study groups.

Minimization will be conducted using a SAS (Cary, NC, USA) macro (Additional file 1). The generic two-group SAS macro for minimization [73] was adapted into the three-group algorithm by [name] and [name] (personal communication, March 2011).

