### Analysis

Differences in the primary and secondary outcomes between the three groups will be determined using non-parametric tests. Multi-group differences in the rate of pharmacotherapy escalation will be determined using the Kruskal-Wallis test. Differences in the proportion of participants with disease progression will be compared using the Cochran-Mantel-Haenszel test with continuity correction. Two-group differences will be tested using the Wilcoxon Rank Sum (Mann–Whitney U) test. Correction for multiple comparisons will be conducted using the Tukey method.

The primary analysis population will be intent-to-treat. As-treated and per-protocol study populations will also be reported. In the intent-to-treat analysis, the minimization algorithm will be preserved and dropouts will be assumed to have had no progression post-dropout. In the as-treated analysis, patients misallocated relative to the minimization algorithm will be analyzed per the intervention received. In the per-protocol analysis, misallocated participants and other protocol violations specified prior to breaking the blind will be omitted. Complete and Markov chain Monte Carlo multiple imputed data will be reported. The goal of analyzing across different analysis sets is to demonstrate robust study results across the various alternatives. All statistical analyses will be conducted using SAS/STAT version 9.2 (Cary, NC, USA).

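### Clinical, function and quality-of-life secondary outcomes are compared as unadjusted changes from baseline, which gives up precision that the collected week-0 values could supply

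*Protocol article*

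**What the plan says.** The protocol article, Outcomes, Secondary outcomes, lists disease activity, function, quality-of-life and imaging measures and states: "Changes from baseline over biannual time points will be investigated". It adds: "All secondary outcomes are exploratory and therefore hypothesis-generating in nature".

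The Analysis section gives the test family: "Differences in the primary and secondary outcomes between the three groups will be determined using non-parametric tests". For pairs of arms: "Two-group differences will be tested using the Wilcoxon Rank Sum". The Kruskal-Wallis test is named for one outcome only: "Multi-group differences in the rate of pharmacotherapy escalation will be determined using the Kruskal-Wallis test". The same section reports both complete and multiply imputed data. No section adjusts a comparison for a baseline value. The remark that the minimization algorithm is preserved under intent-to-treat reads as analysis by allocated arm, not as covariate adjustment.

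Table 1 (Interventions) schedules joint counts, global impressions, ESR, CRP and the HAQ at week 0, and also the row "Health Utility Index Mark 3 and EQ-5D". Under Randomization, DAS28 (in four bands) and the HAQ are minimization factors, among those described as prognostic.

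**The concern.** A change score subtracts the whole baseline reading, including its measurement noise and day-to-day variation. Adjusting for baseline instead subtracts only the part that predicts follow-up. When the two readings are imperfectly correlated, the change score is the noisier of the two, and a rank test on it makes no further use of the baseline.

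The trial is sized on treatment escalation, and the article claims no power for any secondary outcome. Comparisons of disease activity, function and quality of life therefore have no planned precision to spare. They are meant to generate hypotheses, and for that the useful product is a reasonably tight estimate. Minimizing on DAS28 and HAQ limits chance imbalance in those two, but the precision is recovered only if the analysis also uses them.

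**Working it through.** **The plan's own figure.** There is none for the secondary outcomes. The only sample size is for escalation. Its inflation step reproduces: 45 / (0.95 × 0.85 × 0.95²) = 61.7, so 62 per arm. I use 62 only as the arm size.

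**Inputs.** 62 per arm (Sample size). The baseline-to-follow-up correlation ρ is not in the document, so 0.3 to 0.8 is assumed.

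**Variance.** Let σ₀ and σ₁ be the baseline and follow-up standard deviations.

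- Change score: σ₀² + σ₁² − 2ρσ₀σ₁
- Baseline-adjusted: σ₁²(1 − ρ²)
- Difference: (σ₀ − ρσ₁)², which is never negative

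With σ₀ = σ₁ the ratio of adjusted to change is (1 − ρ²) / [2(1 − ρ)] = (1 + ρ)/2.

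Take a two-arm effect that the change score would detect with 80% power (two-sided 5%). The adjusted analysis then has power Φ(2.80/√ratio − 1.96). For example, at ρ = 0.5: 2.80/0.866 − 1.96 = 1.27, giving 90%.

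| ρ (assumed) | Variance ratio | Fall in standard error | Change-score n per arm to match 62 adjusted | Adjusted power where change has 80% |
|---|---|---|---|---|
| 0.3 | 0.65 | 19% | 62/0.65 = 95 | 94% |
| 0.5 | 0.75 | 13% | 62/0.75 = 83 | 90% |
| 0.7 | 0.85 | 8% | 62/0.85 = 73 | 86% |
| 0.8 | 0.90 | 5% | 62/0.90 = 69 | 84% |

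**Simulation with the named pairwise test** (62 per arm, 2,500 runs per setting, effect set as above):

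| Data | ρ | Wilcoxon on change | Rank ANCOVA | ANCOVA |
|---|---|---|---|---|
| Normal | 0.3 | 78% | 93% | 94% |
| Normal | 0.5 | 77% | 88% | 90% |
| Normal | 0.7 | 78% | 84% | 87% |
| Normal | 0.8 | 78% | 78% | 83% |
| Skewed (gamma) | 0.3 | 87% | 97% | 93% |
| Skewed (gamma) | 0.5 | 87% | 93% | 89% |
| Skewed (gamma) | 0.7 | 87% | 89% | 86% |
| Skewed (gamma) | 0.8 | 86% | 84% | 84% |

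The fair comparison with the plan is rank test against rank test. On normal data the gain is about 15, 11, 6 and 0 points. On skewed data it is about 10, 7 and 2 points, then a loss of about 2. The ANCOVA column also includes the switch from a rank to a parametric test.

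**Three arms.** With 53 per arm (62 × 0.85), normal data and assumed effects of 0, 0.25 and 0.5 SD, an omnibus rank test on change has 46%, 60%, 82% and 95% power for ρ of 0.3, 0.5, 0.7 and 0.8. Rank ANCOVA has 66%, 72%, 87% and 96%. Null rejection stayed between 3.5% and 6.0%.

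**Accumulating imaging scores.** If follow-up equals baseline plus independent progression, the regression of follow-up on baseline has slope 1, so ρσ₁ = σ₀ and the variance difference above is zero. A simulation of skewed scores built this way (53 per arm, 1,500 runs) agrees. Rank ANCOVA against Kruskal-Wallis on change gave 42% against 41% at ρ = 0.3 and 42% against 39% at ρ = 0.9. Ordinary ANCOVA equalled the change-score F-test (54% each).

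**The case against.** The strongest reply is that these outcomes are exploratory, that the article condenses a fuller plan, and that covariates for such outcomes are often left to that plan. In part this stands: it limits the weight of the point. It does not remove it, because the article states both the metric (change) and the test family, and the pairwise test it names takes no covariate.

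Several stronger readings are tempting and are not supported:

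- **That every secondary outcome loses power.** The gain fades as ρ rises and is small or absent for skewed, accumulating imaging scores. For imaging, change in multiples of the smallest detectable difference is also the trial's own definition of progression.
- **That participants missing a visit are simply lost.** The Analysis section also reports multiply imputed data, so this would apply only to the complete-data analysis.
- **That each visit is tested separately, or by Kruskal-Wallis.** The article does not say the first, and it names Kruskal-Wallis only for escalation. The argument needs only an unadjusted rank test on change.
- **That the week-13 and week-39 data are wrongly wasted.** The article says "Clinical assessments, prognosis, and response to pharmacologic treatment will be assessed quarterly during the first year and biannually in the second", but it deliberately sets the secondary comparisons at biannual points. What the extra visits would add has not been quantified.
- **That these outcomes are the only evidence of benefit.** Imaging progression is a co-primary endpoint. The statement is true only if benefit means disease activity, function or quality of life.

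**Conclusion.** The point holds for the continuous clinical, function and quality-of-life indices, as a matter of precision only. The stated analysis compares unadjusted changes by rank although the baseline values are collected. Under equal variances the avoidable excess is such that adjustment leaves 65% to 90% of the change-score variance over ρ of 0.3 to 0.8. Within rank methods, the two-arm power gain on normal data runs from about 15 points at ρ = 0.3 to none at 0.8.

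The size rests on assumed correlations, effects and distributions, none of which the article gives. A reader might infer bias or a threat to the main result. Neither follows: randomized comparisons of change are unbiased, and the escalation analysis and its sample size are unaffected. Some listed instruments, such as the Multi-Dimensional HAQ, are not named in Table 1, so their week-0 collection is inferred from the plan to analyse change. This is a worthwhile low-cost improvement, not a flaw that endangers the trial.

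**What to change.** In the Secondary outcomes and Analysis sections, for the disease activity, function and quality-of-life indices, state that follow-up values are compared between arms adjusted for the participant's own baseline value. Rank analysis of covariance does this and stays within the non-parametric plan. Where the distribution is roughly symmetric, ANCOVA or a repeated-measures model is an alternative. Name the choice for each outcome before the blind is broken. Keep the planned multiple-imputation analysis, and keep raw changes for description of these indices.

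For vdHSS and RAMRIS, leave the change-based analysis in place and offer baseline-adjusted rank analysis as an optional supplement.

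The cost is wording and a little more analysis work, with no new data. A parametric model brings its distributional assumption and, for repeated measures, a missing-at-random assumption; the rank version avoids the distributional one.

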### Randomization

Minimization (that is, baseline adaptive randomization) will be used to allocate participants to one of the three study interventions. Allocation by minimization is recommended for small sample size clinical trials in diseases with many known prognostic markers [41,42]. The minimization procedure can accommodate 10 to 20 variables without sacrificing statistical power [71,72]. Parameters for minimization will include the following:

● Participant self-reported symptom duration (<6, 6-24, >24 months)

● Baseline 28-joint Disease Activity Score (<2.6, 2.6-3.2, 3.2-5.1, >5.1)

● MRI or X-ray evidence of erosions from the hands, wrists or feet at baseline

● Rheumatoid factor positivity (positive; negative; not available)

● Anti- citrullinated cyclic peptide positivity (positive; negative; not available)

● Extra-articular features of RA

● Health Assessment Questionnaire

● Conventional DMARD treatment

● Biologic DMARD treatment

● Treating rheumatologist

With the exception of 'treating rheumatologist', these variables have prognostic value and are expected to inform DMARD treatment decision-making [43]. ‘Treating rheumatologist’ will be included as a minimization parameter to balance the effect of varying pharmacological disease management standards of care by physician across the three study groups.

Minimization will be conducted using a SAS (Cary, NC, USA) macro (Additional file 1). The generic two-group SAS macro for minimization [73] was adapted into the three-group algorithm by [name] and [name] (personal communication, March 2011).

### Blinding

Study personnel involved with participant follow-up, care, outcome assessments, or statistical analyses will be blinded to the randomization scheme. Upon determination of eligibility, consent, and value of the minimization parameters for the participant, the enrolling study personnel will place a telephone call to the central study coordinator for the randomization of the participant. Centrally, data entry will be audited in real-time to ensure accuracy. The central study coordinator will assign a randomization number to the participant, record this number on the randomization scheme and report the number to the enrolling study personnel. The caller will record the randomization number in the participant’s case report form.

The MRI and X-ray images will be anonymized, such that direct comparisons between MRI or X-ray images for the same participant and time point, or images for the same participant from the same modality over time cannot be compared. All radiologists’ assessments will be reported back to the unblinded central study coordinator. The central coordinator will then process the results of the radiologists’ assessments based on the intervention allocation of the participants. Blinded disease progression results will be reported back to the study rheumatologist.

### Allocation concealment

The intervention allocation scheme will be concealed from all study participants and study personnel involved in care for participants. Access to the minimization scheme for treatment allocation will be limited to the central unblinded study coordinator or designate. This coordinator will not be involved with the clinical assessment of study subjects or intervention implementation. Statistical analysis will be blinded to treatment allocation.

### Statistical analysis

#### Sample size

A sample size of 186 RA and UIA patients was estimated from a one-way analysis of variance statistical test to determine a difference in the rate of pharmacological treatment escalation between imaging interventions over 2 years between three groups with intermediate dispersion of data [74].

(3)$$f=\frac{d}{2}\sqrt{\frac{\left(k+1\right)}{3\left(k-1\right)}}$$

where *f* is the analysis of variance effect size; *k* is the number of groups being compared; and *d* is the standardized effect size,

(4)$$d=\frac{\delta }{s}$$

where, *δ* is the difference between the greatest and least group mean; and *s* is the standard deviation.

This parametric test is sufficiently robust to yield sample size estimates for non-parametric data [74].

Treatment escalation was assumed to be directly proportional to disease progression. The rate of X-ray progression over 2 years [75] was taken together with 1-year MRI and X-ray progression data [15] to estimate testing between 36% MRI progression of the second to fifth MCPs joints of a single hand, 25% radiographic progression of bilateral hands and wrists, and no progression for the standard of care group. Although some patients may progress several-fold over the clinically relevant threshold, progression was conservatively assumed to result in a single pharmacological treatment escalation per affected participant, since a change in therapy is expected to introduce an incremental protective effect.

The estimated standard deviation around disease progression-related treatment escalation rates was assumed to vary proportionally the variance around disease progression. From Emery and colleagues (2009), an average standard deviation of 5% greater magnitude than the mean progression was determined for group sample sizes of approximately 200 [75]. Standard deviation is inversely related to . A sample size 25% greater than the mean effect size reported in Emery was estimated here. Therefore, *δ* ≈ 0.46 and *s* ≈ 0.58, *f* ≈ 0.33. This represents a sample size of ≈ 45 per group [74] unadjusted for spontaneous remission, attrition and missing data. Despite the liberal inclusion criteria used here, with the current setting characterized by patients with significantly progressed symptom duration, spontaneous remission was conservatively estimated at 5%. Missing data and annual attrition were estimated to be 15% and 5%, respectively. Given these estimates, a sample size of 62 participants per intervention allocation group will be required to determine a 36% difference in the rate of treatment escalation with 90% power at a 5% level of significance [74,76]. A total of 186 IA patients will be recruited by six participating rheumatologists.

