Limiting disease progression on diagnostic imaging remains an important clinical and regulatory outcome [34]. Early pharmacologic treatment of RA with conventional and biologic disease-modifying anti-rheumatic drugs (DMARDs) has proven to improve clinical [35-38] and radiological [38] outcomes. Treat-to-target strategies of maintaining low disease activity using anti-rheumatic drug augmentation have also been demonstrated to improve clinical outcomes in patients [39]. Despite optimal control of clinical and laboratory findings, erosive disease progression may continue to progress for subsets of the disease population [17]. These data suggest that diagnostic imaging may complement pharmacotherapeutic decision-making. However, diagnostic imaging is infrequently and unsystematically applied to routine disease management [40]. Disease monitoring with sensitive and responsive imaging modalities may help to augment therapy and further delay disease progression.

The primary objective of the study is to investigate the relative value of MRI or X-ray over standard of care as tools to guide DMARD treatment decision-making by rheumatologists for the care of RA and UIA. Specifically, the study compares the effect of biannual monitoring of disease progression with: 1) 1.0 T extremity MRI of the second to fifth metacarpophalangeal joints (MCPs) of the worst-affected hand at baseline; 2) X-rays of both hands and wrists; and 3) standard of care on the rate of augmenting DMARD treatment decision-making over 2 years. The co-primary objective aims to determine differences in diagnostic imaging evidence of disease progression with biannual monitoring using MRI or X-ray over standard of care over 2 years.

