Second, the relative merits of MRI and X-ray as prognosticators in RA and UIA will be determined. The increased sensitivity of MRI for erosions that arise from the direct paired-bone comparisons is evident [14-17,29,30] but must be tempered by the increased false-positive rate for MRI erosions in healthy controls [47,81-83]. When the anatomies commonly imaged in practice are compared, the relative merits are less clear [14,15]. The probability of erosion is uniform neither by patient nor joint. In active disease, substantial erosive changes were noted in many patient joints, while others were spared [84]. These findings set the expectation that the greater number of bones and joints imaged on X-ray may negate the increased sensitivity of MRI in fewer joints. The advantages to imaging a greater number of joints needs to be taken into consideration with the increased demand on patients, cost, and false-positive rate. Further, the features measured for the X-ray and MRI interventions include more than just erosions and differ by modality. In RAMRIS, erosion score accounts for more than 69% of the total potential score [24]. The other MRI features measured are more transient than erosions and account for a minority of the total potential score: synovitis, the most transient, accounts for up to 10% of the total RAMRIS; edema accounts for up to 21% of the total score [24]. In contrast, vdHSS accounts for erosions and JSN. The former accounts 57% of the score for bilateral hands and wrists [45,46]. There is sufficient uncertainty in the relative prognostic merits of MRI and X-ray to argue the position of clinical equipoise in relation to the primary objective.

The merits of the proposed study should to be balanced with its limitations. To this end, the study population may be less than ideal. Challenges exist to adjusting diagnostic imaging evidence of disease progression for measurement reliability. The data used to estimate the sample size requirements were limiting. Other limitations may exist as well. The implications of these limitations and alternatives are discussed below.

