Third, for the sample size calculation, rates of disease progression were conservatively estimated from literature reports of disease progression between MRI and X-ray. Standard of care treatment escalation and a clinically meaningful effect size were not specifically accounted for in the estimate. Despite this limitation, the authors considered the sample size to be sufficient to resolve any incremental benefit of the interventions in the study population investigated.

A number of factors are expected to impact the relative merits of MRI and X-ray as prognostic tools in IA, including those affecting image resolution (for example, magnet strength to bore diameter ratio for MRI; number of views for radiography) and stage of disease. Measurement considerations including number of raters involved, their qualification and experience, number of readings and raters per image set, independent versus paired image rating, blinding the chronological order of image acquisitions, and current anti-rheumatic therapy are expected to affect the MRI and X-ray interventions equally.

This study represents an initial investigation into the clinical utility of MRI and X-ray in guiding anti-rheumatic pharmacotherapeutic decision-making for IA. The work will contribute to the knowledge of how diagnostic imaging may be leveraged to optimize rheumatologic care. Pending findings, future work will investigate the optimization of this intervention strategy, including but not limited to identifying population subsets at greatest risk, adjusting the interval over which imaging is conducted, testing in conjunction with a specific intensive DMARD clinical management strategy, and automated abnormality detection and quantification.

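### The stated 90% power is for the overall three-group test; for the Tukey-corrected pairs that answer the objective, the plan's own figures do not support the claim that the sample can resolve any benefit of imaging

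*Protocol article*

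**What the plan says.** The Sample size section bases the trial on a three-group analysis of variance: "A sample size of 186 RA and UIA patients was estimated from a one-way analysis of variance statistical test". The effect size f is built from δ, the gap between the highest and lowest arm mean. The planning rates are "36% MRI progression of the second to fifth MCPs joints of a single hand, 25% radiographic progression of bilateral hands and wrists", with "no progression for the standard of care group". The section arrives at δ ≈ 0.46, s ≈ 0.58 and f ≈ 0.33, giving about 45 per group, inflated to 62 (186 in all). The Abstract and the Sample size section attach 90% power at the 5% level to a 36% difference.

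The primary objective, at the end of the Background, is to "investigate the relative value of MRI or X-ray over standard of care as tools to guide DMARD treatment decision-making". The Analysis section plans a Kruskal-Wallis test across the three groups and Wilcoxon rank sum tests for pairs, and adds: "Correction for multiple comparisons will be conducted using the Tukey method". No power is given for any pair.

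The Discussion says that "the relative merits of MRI and X-ray as prognosticators in RA and UIA will be determined". On sample size it concludes that "the authors considered the sample size to be sufficient to resolve any incremental benefit of the interventions in the study population investigated".

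**The concern.** A significant overall test shows that some arm differs, not which one. Whether MRI adds to standard of care, and whether X-ray does, can be learned only from the two-group tests. These face a higher threshold than an uncorrected test, and two of the three involve gaps smaller than δ.

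The 90% therefore describes a different test from the ones that carry the modality-specific conclusions. Tying it to a 36% difference makes it read like a promise about a pair. If the arms behave as planned, X-ray versus standard of care could well miss significance, and MRI versus X-ray almost certainly would. A reader relying on the sufficiency statement could then take a null result as evidence of no added value or of equivalence.

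**Working it through.** **Inputs.** From the Sample size section: arm rates 0.36, 0.25 and 0; δ = 0.46; s = 0.58; k = 3; α = 0.05; 45 evaluable and 62 recruited per group; losses of 5% (remission), 15% (missing) and 5% per year for two years. Tukey correction: Analysis section. Pairwise tests are taken as two-sided.

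**1. The plan's own figure.**
- d = 0.46/0.58 = 0.793.
- f = (0.793/2) × √(4/6) = 0.324 (printed ≈ 0.33).
- Noncentral F with 2 and 132 degrees of freedom and noncentrality 0.324² × 135 ≈ 14.2 gives power 92.5% at 45 per group.
- 45/(0.95 × 0.85 × 0.90) = 61.9, hence 62, and 3 × 62 = 186.

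The overall-test calculation reproduces, slightly above 90%.

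**2. Pairwise power on the same inputs.** Noncentral t with noncentrality (difference/s) × √(n/2), against the Tukey critical value (studentized range/√2): 2.370 at n = 45 and 2.363 at n = 62.

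The printed δ of 0.46 exceeds the printed 36% gap by 0.46/0.36 = 1.278. To put the other gaps on the scale of δ: 0.25 × 1.278 = 0.319 and 0.11 × 1.278 = 0.141. The means 0, 0.319 and 0.46 give f = 0.332, close to the printed value, so the scaled rows are the more coherent reading.

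| Comparison | Difference | n = 45 | n = 62 |
|---|---|---|---|
| MRI vs standard of care | 0.46 (δ) | 91.6% | 97.9% |
| MRI vs standard of care | 0.36 (printed) | 71.6% | 86.2% |
| X-ray vs standard of care | 0.319 (scaled) | 59.6% | 75.9% |
| X-ray vs standard of care | 0.25 (unscaled) | 37.5% | 51.6% |
| MRI vs X-ray | 0.141 (scaled) | 11.5% | 15.8% |
| MRI vs X-ray | 0.11 (unscaled) | 7.4% | 9.8% |

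Example: 0.319/0.58 × √22.5 = 2.61, against 2.37, gives 59.6%.

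The intermediate-dispersion formula itself places X-ray midway, at 0.23 from each neighbour. Both smaller contrasts then have 32% [44%].

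**3. Sensitivity to the SD.** The section assumes one escalation per affected patient. Read as a 0/1 outcome, its SD cannot exceed 0.5, so s = 0.58 is too large. Simulation with Tukey-level critical values at 45 per group gives:
- X-ray 25% vs 0%: about 98% (about 86% if the variance is pooled across arms).
- X-ray vs standard of care if 10–50% escalate under standard of care and X-ray adds 25 points: about 50–71%. The 10–50% is an assumption; the document gives no rate.
- MRI vs X-ray: about 9–14% (at most about 22% with pooled variance and no escalation under standard of care).

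**4. The closed alternative.** With three groups, an overall test at 5% followed by each pair at unadjusted 5% holds the familywise error at 5%. In normal-data simulation at 45 per group and s = 0.58, X-ray versus standard of care rises from 37.5% to about 50% (unscaled), or from 59.6% to about 73% (scaled).

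**The case against.** The sample-size arithmetic is sound on its own terms, and the analysis of variance corresponds to a test that is actually planned, the Kruskal-Wallis test. The Abstract does mention three groups. All of this stands: a reader might infer that the sample size is miscalculated or matches no planned test, and the document does not support that. But the overall test cannot answer the objective as worded.

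The X-ray shortfall is model-dependent. The 37.5% sets an unscaled difference against the SD that goes with δ = 0.46, so it should not be the headline; about 60% is the fairer figure. With a 0/1 outcome and no escalation under standard of care, the shortfall disappears. This also stands. However, the Discussion concedes that escalation under standard of care was left out of the estimate and expects it to dampen the signal, so a zero rate is the optimistic end.

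MRI versus X-ray is partly exploratory. The secondary objectives include the difference in changes detected by the two modalities, paired analyses are planned, and every patient has both scans. The sentence on relative merits as prognosticators may therefore mean the within-patient comparison. That is fair, and the low power here concerns only the between-arm escalation comparison. A reader might credit that comparison with about 20% power, but this is the uncorrected figure at 0.141; with Tukey it is about 12%.

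Finally, nothing in the protocol says a null result will be read as equal merit. That is a risk created by the wording, not a stated plan.

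**Conclusion.** The concern holds in limited form. The 90% (92.5% at 45 per group, δ = 0.46, s = 0.58) is overall power. After Tukey correction, only MRI versus standard of care at δ = 0.46 keeps about that level, and it falls to 72% [86% at 62 per group] at the printed 36%.

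X-ray versus standard of care has about 60% [76%] on scaled inputs. That conclusion rests either on the plan's SD or on some escalation under standard of care; it would be wrong to say that the X-ray comparison is underpowered whatever the outcome model. Between-arm MRI versus X-ray is far below 90% under every model examined.

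The sufficiency statement in the Discussion therefore goes beyond what the plan's own inputs support. The figures above are normal-theory values except where a 0/1 outcome is stated; the planned rank tests would do slightly worse on normal data.

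**What to change.** - **Abstract and Sample size:** state that the 90% applies to the overall three-group test at δ = 0.46, and print the three pairwise powers beside it with their assumed differences and SD.
- **Discussion:** limit the sufficiency claim to the overall test and to MRI versus standard of care at that δ. State that the between-arm MRI versus X-ray escalation comparison is reported as an estimate with its confidence interval and that non-significance is not read as equal merit.
- **Analysis:** replace the Tukey correction with the closed procedure: Kruskal-Wallis at 5% and, only if significant, each pairwise Wilcoxon test at unadjusted 5%. Settle this before the blind is broken.

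The cost is a less favourable stated power for two of the three contrasts and the loss of Tukey simultaneous confidence intervals. The closed procedure is a change of method, not only of wording, but it needs no extra patients or procedures. It does not rescue MRI versus X-ray, which has only 14–21% at 45 per group even with no correction.
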